## **Abstract**

**Introduction:** Warfarin is a narrow therapeutic index drug that requires frequent monitoring using the international normalized ratio (INR). Current clinic-based INR monitoring models lead to suboptimal warfarin management. Warfarin patient self-management (PSM) has consistently demonstrated superior efficacy compared to clinic-based management but is virtually unused in the US healthcare system. The objective of this study is to implement PSM in the US healthcare system using strategies developed to overcome previously identified barriers associated with PSM underutilization as well as potential PSM facilitators.

**Methods and analysis:** We aim to implement PSM with 150 adult patients at four sites using strategies developed to address barriers to PSM specific to the US healthcare system. Implementation strategies will be guided by the Consolidated Framework for Implementation Research and the Quality Implementation Framework supported by Rapid Cycle Research Methodology. A type III hybrid implementation-effectiveness study design will be used to assess PSM implementation strategy outcomes while also gathering information on PSM clinical outcomes centered on the five elements of the RE-AIM framework (Reach, Effectiveness, Adoption, Implementation, Maintenance). This study will be approved by the ethics boards at all participating sites.

**Discussion:** We plan to disseminate the results of this research program examining the feasibility of PSM in US anticoagulation management services in scientific journals and conferences, as well as making elements of the PSM implementation toolkit publicly and freely available.

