#### *Reach*

The primary implementation outcome (the percentage of consented participants successfully transitioned to PSM) will be calculated using the following denominators 1) all patients receiving warfarin; 2) all patients invited to participate in the study and attempt PSM including those who decline participation; and 3) all participants who provide informed consent and attempt transitioning to PSM. Successful transition to PSM will be defined as completing 6-months of PSM. The timing of PSM transition failures during the 6-month follow-up period will be recorded. Reasons patients refuse to participate in PSM implementation activities and reasons patients failed to successfully transition to PSM during implementation efforts will be recorded and categorized.

Data for “reach” outcomes will be summarized using descriptive statistics. Differences in baseline characteristics between eligible patients who do and do not agree to participate in the PSM implementation phase and between those who do and do not successfully transition to PSM will be compared using the chi-squared test of association (categorical variables), Fisher’s

exact test (categorical variables that occurred infrequently) or Student's t-test (continuous variables). Two-sided p-values <0.05 will be considered statistically significant.

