### *Effectiveness*

The following INR control outcomes will be compared between eligible participants who do and do not successfully transition to PSM during the 6-month follow-up period, 1) individual time in the therapeutic INR range (TTR) using linear interpolation; and 2) proportion of INRs resulting in a warfarin dose change. INR control outcomes will also be compared between the 6-month periods before and after PSM transition attempts (Figure 2).

Additional effectiveness outcome comparisons before and after PSM transition will include major bleeding and clinically relevant non-major bleeding events as defined by the International Society on Thrombosis and Haemostasis, thromboembolic events, and all-cause mortality. Thromboembolic events will include stroke, systemic embolism or venous thromboembolism documented by objective imaging. Bleeding and thromboembolic events will be confirmed by manual EHR review. For participants who successfully transition to PSM, AKT, ACT, and SF-36 scores will be compared before and after PSM transition.

Data analysis for "effectiveness" outcomes will consist of basic descriptive statistics. T-tests and the chi-squared test of association will be used to compare differences in continuous and categorical outcomes between patients who do and do not successfully transition to PSM during the 6-month PSM phase. Paired t-tests and McNemar's test will be used to compare differences between continuous and categorical outcomes before and after PSM transition, respectively. Two-sided P-values <0.05 will be considered statistically significant.

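### The before/after test of all-cause mortality is uninformative by design, because nobody enrolled can have died in the before period

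*Protocol*

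**What the plan says.** All of the following is in the protocol. The Effectiveness section introduces the clinical events with "Additional effectiveness outcome comparisons before and after PSM transition will include major bleeding", and that list ends with "thromboembolic events, and all-cause mortality". For the analysis it states: "Paired t-tests and McNemar's test will be used to compare differences between continuous and categorical outcomes before and after PSM transition, respectively". The threshold follows: "Two-sided P-values <0.05 will be considered statistically significant". Mortality is not exempted from the test or the threshold.

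The windows are given for the anticoagulation-control outcomes: "INR control outcomes will also be compared between the 6-month periods before and after PSM transition attempts". The event sentence gives no window of its own, so I take the same six months on each side.

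The Reach section defines success: "Successful transition to PSM will be defined as completing 6-months of PSM". The Abstract gives the size: "We aim to implement PSM with 150 adult patients at four sites".

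**The concern.** A paired before/after test needs an outcome that can occur in either period. Death cannot. The cohort is assembled from people alive at the end of the before period, so the comparison sets a period with guaranteed survival against one without.

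Any deaths that occur in the ordinary course of follow-up will then look like a deterioration after PSM began. The Background section cites lower mortality as one of the reasons for PSM, and this test could never show such a benefit. The Discussion also promises evidence on whether US patients can manage themselves safely. A mortality p-value driven by background death rates would mislead on that question.

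**Working it through.** **Inputs from the protocol.** n = 150 (Abstract); McNemar's test, two-sided 0.05 (Effectiveness); six-month windows (Effectiveness, stated for INR control and assumed here for deaths). Patients are screened, consent and complete a baseline survey before PSM begins (Recruitment process; PSM implementation phase), and must already have taken warfarin for over nine months (Patient selection criteria).

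**Input not in the protocol.** Six-month mortality. I assume 0.5% to 4% and show the range. The protocol states no power or event-rate figure for mortality, so there is nothing to reproduce.

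**Step 1: the paired table.** Let b be the pairs with death before only and c the pairs with death after only. Nobody who died before can be enrolled, so b = 0. Pairs with death in both periods are impossible too. This leaves c deaths after and 150 − c pairs with no death. A death during the supervised run-in does not change this: if the after period starts later, that person has no after period to pair.

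**Step 2: the test with b = 0.**
- Uncorrected: χ² = (b − c)²/(b + c) = c, on 1 df.
- Continuity-corrected: χ² = (c − 1)²/c.
- Exact two-sided: p = 2 × 0.5^c, capped at 1.

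| Deaths after (c) | Uncorrected p | Corrected p | Exact p |
|---|---|---|---|
| 1 | 0.317 | 1.00 | 1.00 |
| 2 | 0.157 | 0.480 | 0.50 |
| 3 | 0.083 | 0.248 | 0.25 |
| 4 | 0.0455 | 0.134 | 0.125 |
| 5 | 0.025 | 0.074 | 0.0625 |
| 6 | 0.014 | 0.041 | 0.031 |

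The uncorrected test is significant from 4 deaths, the corrected and exact tests from 6. The protocol does not say which version applies.

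**Step 3: chance of a significant increase when PSM does nothing.** This is P(X ≥ 4) or P(X ≥ 6) for X ~ Binomial(150, m), where m is the assumed six-month mortality.

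| Assumed m | Expected deaths (150 × m) | Uncorrected (≥ 4) | Exact (≥ 6) |
|---|---|---|---|
| 0.5% | 0.75 | 0.7% | 0.01% |
| 1% | 1.5 | 6.5% | 0.4% |
| 2% | 3.0 | 35.3% | 8.2% |
| 3% | 4.5 | 66.2% | 29.6% |
| 4% | 6.0 | 85.4% | 55.8% |

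McNemar's null hypothesis, equal probability of death in the two windows, is false by construction whenever anyone can die in follow-up. Rejecting it therefore says nothing about PSM.

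**Step 4: is there another mortality comparison to fall back on?** The same section compares those who do and do not transition successfully. Success means completing six months, so anyone who dies within that time is a failure by definition and all deaths fall in one group. No external or concurrent comparator is named for the before/after mortality comparison.

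**The case against.** The best reply concerns weight. This is a feasibility study whose primary outcome is the percentage transitioned. Mortality comes last in a list of additional outcomes, with no hypothesis, sample-size basis or decision rule attached. The analysis paragraph opens with descriptive statistics and names McNemar's test for categorical outcomes generally, not for death. Table 3 schedules pre-study and post-study chart review for bleeding and thromboembolism and has no mortality row. Patients are selected for medical stability, which points to low mortality. At 1% the exact test would reject far less often than 5% of the time, and with one to three deaths no version reaches 0.05. All of this stands, and it lowers the importance of the point. It does not make the comparison meaningful: the protocol names the outcome, the contrast, the test and the threshold.

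Three stronger readings are tempting but not supported.
- **Completers only.** A reader might infer that the comparison covers only people who finish six months of PSM, so that deaths are zero in both windows and the test is undefined. The Effectiveness section applies that restriction to the survey scores only. It refers to transition attempts for INR control and to neither for events. This is the less likely reading.
- **The bleeding and thromboembolism comparisons fail in the same way.** Fatal events cannot occur before enrolment, but non-fatal ones can occur in both windows. The protocol gives no fatal fraction from which to size the bias, which is smaller in kind.
- **A high false-positive rate is certain.** The 85.4% needs both 4% mortality, which is an assumption, and the uncorrected test, which the protocol does not specify.

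**Conclusion.** The point holds for mortality. As written, the before/after test has one discordant cell fixed at zero, so it can only suggest harm or show nothing. That conclusion follows from the protocol alone.

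Its size depends on assumed mortality, on the version of the test, and on all 150 planned participants contributing a full after window. From 1% to 4% mortality, the chance of a spurious significant increase runs from 6.5% to 85.4% uncorrected and from 0.4% to 55.8% exact. Below about 1% the result would be uninformative more often than misleading.

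A reader might infer that the study's main result is compromised. It is not: the primary implementation outcome, INR control and the survey scores do not depend on this test. The correction is worth making before analysis, but it ranks below a must-fix.

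**What to change.** Remove all-cause mortality from the before/after comparisons. Report deaths during follow-up among everyone who started the transition, whether or not they completed it, as a count and a rate per person-time with an exact 95% confidence interval, and state the date from which follow-up counts.

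As an illustration, Clopper-Pearson limits are 0 to 2.4% for 0/150 and 0.4% to 5.7% for 3/150. If all 150 were followed for six months (150 × 0.5 = 75 person-years) with no deaths, the exact upper limit would be −ln(0.025)/75 = 3.69/75, or 4.9 per 100 person-years.

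Also state that the before/after bleeding and thromboembolism comparisons include all who started. Listing fatal events separately there is an optional, smaller refinement.

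The cost is a wording change and the loss of one p-value that could not be interpreted. No additional patients are needed.

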#### PSM implementation phase

Prior to initiating PSM, consenting participants will complete an online survey hosted in REDCap containing the following: 1) the anticoagulation knowledge tool (AKT), a validated 28-item instrument that assesses participants' anticoagulation knowledge; 2) the anti-clot treatment scale (ACTS), a 15-item participant-reported instrument assessing satisfaction with anticoagulant treatment that includes a 12-item Burdens scale and a 3-item Benefits scale; and 3) the Short Form 36 questionnaire (SF-36), a validated instrument used to estimate health-related quality of life.

Participants will complete the previously described interactive online educational module in preparation for initiating PSM. Clinician study team members at each site will use the combination of each participant's PSM knowledge assessment score, comfort level with PSM, and their subjective assessment of the participant's likelihood of success with PSM to determine if they should progress to the "spotters ready" phase where clinicians will provide feedback on the participant's warfarin dosing plans as needed. The "spotters ready" phase will end and the formal PSM phase begin once participants express feeling comfortable starting PSM on their own.

During the 6-month PSM phase, participants will be asked to check INRs every 1 to 2 weeks when INRs are in range and weekly when INR are out of range. Participants will be asked to use clinical decision support tools from the implementation toolkit (My Warfarin, DIY) or use their own experience to make independent warfarin dosing decisions. Participants will be asked to contact clinicians in high-risk situations as previously described or when additional advice is desired.

During the PSM phase, participants will self-report INR results, warfarin dosing decisions, the method used to arrive at dosing decision (i.e., My Warfarin, DIY, or using their own judgement), factors potentially impacting INR response (i.e., changes in other medications, diet, and/or health status), and bleeding/ thromboembolic complications using the previously described online data collection form hosted in REDCap.

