| Baseline characteristics                     |           | X          |           |            |            |
| Bleeding/thromboembolic event chart reviews  | X         |            |           |            | X          |
| Pre-study INRs & warfarin doses              | X         |            |           |            |            |
| Patient                               |           |            |           |            |            |
| Baseline survey                              |           | X          |           |            |            |
| Education module                             |           | X          |           |            |            |
| Spotters ready INR surveys                   |           |            | X         |            |            |
| PSM INR surveys                              |           |            |           | X          |            |
| Post-study survey                            |           |            |           |            | X          |

349 PSM-patient self-management; INR-international normalized ratio

350

|                                                                                   |                                                                                                                                                             |
|-----------------------------------------------------------------------------------|-------------------------------------------------------------------------------------------------------------------------------------------------------------|
| [figure not shown] | Recruit prospective PSM patients who were already self-testing INRs using home INR machines                                                          |
| [figure not shown] | Screen potential PSM patients using established patient-clinician relationships                                                                      |
| [figure not shown] | Provide PSM patient education using an interactive online module                                                                                     |
| [figure not shown] | Provide an online data collection form for patients to self-report INR results, warfarin dosing decisions, and bleeding/thromboembolic complications |
| [figure not shown] | Facilitate transition to PSM using a “spotters ready” phase (2-4 weeks) with clinicians until patients confident to fully assume PSM responsibility  |

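### The between-group TTR t-test leaves out the pre-study TTR the trial can already compute, so earlier differences in INR control can appear as a transition-group difference and precision is lost

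*Protocol*

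**What the plan says.** All references are to the protocol.

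- **Outcome.** The Effectiveness section lists "individual time in the therapeutic INR range (TTR) using linear interpolation" first among the INR control outcomes, followed by the proportion of INRs that lead to a dose change.
- **Groups.** These outcomes are "compared between eligible participants who do and do not successfully transition to PSM during the 6-month follow-up period". The Reach section fixes the grouping: "Successful transition to PSM will be defined as completing 6-months of PSM".
- **Between-group test.** "T-tests and the chi-squared test of association will be used to compare differences in continuous and categorical outcomes", judged at a two-sided 0.05 level. No covariate is named.
- **Within-person test.** INR control is also compared between the 6 months before and the 6 months after the transition attempt: "Paired t-tests and McNemar's test will be used to compare differences between continuous and categorical outcomes before and after PSM transition, respectively".
- **Data in hand.** Table 3 has the study coordinator collect "Pre-study INRs & warfarin doses". The patient selection criteria require more than 9 months of prior warfarin, so a 6-month baseline can be formed. Site and goal INR range are recorded in the REDCap survey.
- **How the groups arise.** Under PSM implementation phase, clinicians decide who progresses from the knowledge score, comfort level and "their subjective assessment of the participant's likelihood of success with PSM". The Reach section says that baseline characteristics "between those who do and do not successfully transition to PSM will be compared", one variable at a time.

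**The concern.** The two groups are formed by selection and by staying the course, not by randomisation. People whose INR was steadier before the study may be more likely to complete 6 months of self-management. If so, a test on follow-up TTR alone reports part of that earlier steadiness as a difference between transition groups. Nothing from the Reach comparison of baseline characteristics feeds into the TTR test, and the only multivariable model in the protocol (Adoption section) concerns willingness to participate.

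Even if the groups start level, pre-study TTR probably predicts follow-up TTR. Leaving it out makes the standard error larger than it need be, in a study where the group that does not transition may be small. Because the protocol itself names the test and the significance rule, this is not a detail left open for a statistical analysis plan.

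**Working it through.** **No figure to reproduce.** The protocol gives no SD, effect size, power or expected split for TTR; 150 is a planned enrolment only. What follows is an illustration.

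**Inputs from the protocol:** N = 150; two-sided alpha 0.05; unadjusted t-test.

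**Assumptions, not in the protocol:** TTR SD 20 points in each period; pre/post correlation r = 0.3, 0.5 or 0.7; pre-study gap D = 0, 5 or 10 points; 70% to 90% complete PSM (main case 120 vs 30).

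**Step 1: precision with no baseline gap.**

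SE of the t-test = SD × √(1/n1 + 1/n0) = 20 × √(1/120 + 1/30) = 4.08. The difference detectable with 80% power is (1.96 + 0.84) × 4.08 ≈ 11.4 points.

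SE adjusted for pre-study TTR = SD × √(1 − r²) × √(1/n1 + 1/n0 + D²/((N − 2)SD²)). At D = 0:

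| r | Adjusted SE | Reduction | Detectable difference |
|---|---|---|---|
| 0.3 | 3.89 | 5% | 10.9 |
| 0.5 | 3.54 | 13% | 9.9 |
| 0.7 | 2.92 | 29% | 8.2 |

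With a 10-point gap the adjusted SE is still lower, by 3%, 12% and 27%.

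**Step 2: carry-over of a pre-study gap.** Suppose the groups differ at follow-up only through their pre-study TTR, and the gap regresses by the correlation. The follow-up difference is then r × D. For D = 10 and r = 0.5 it is 5 points against an SE of 4.08, and the normal approximation gives a 23.2% chance of p < 0.05.

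| r | D = 5: carry-over | t-test p < 0.05 | D = 10: carry-over | t-test p < 0.05 |
|---|---|---|---|---|
| 0.3 | 1.5 | 6.6% | 3.0 | 11.4% |
| 0.5 | 2.5 | 9.4% | 5.0 | 23.2% |
| 0.7 | 3.5 | 13.8% | 7.0 | 40.3% |

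For D = 10, a 105/45 split gives 13.4%, 28.9% and 50.2%; a 135/15 split gives 8.5%, 15.1% and 25.1%.

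A simulation of 2,000 trials per scenario at 120/30 agrees: for D = 10 the t-test rejects in 11.3%, 23.1% and 40.1%. The adjusted model rejects in 4.4% to 6.2% across all scenarios.

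**Step 3: how far the adjusted result depends on Step 2's structure.** The near-nominal rate for the adjusted model holds because the gap was made to shrink by exactly r. If the gap instead persists in full, the unadjusted difference is D and adjustment leaves about (1 − r)D. For D = 10 that is 7, 5 and 3 points at r = 0.3, 0.5 and 0.7; for D = 5 it is 3.5, 2.5 and 1.5. Simulated with N = 150, SD 20, r 0.4 to 0.6 and 60% to 80% completing, the rejection rates are:

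| Persisting gap | Unadjusted t-test | Adjusted |
|---|---|---|
| 5 points | 22–33% | 10–17% |
| 10 points | 68–85% | 22–47% |

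Adjustment is better in both structures, but it removes the carry-over only in the first.

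**The case against.** The strongest reply is that the t-test answers the question asked. The Study Design section describes a type III hybrid that mainly evaluates implementation and gathers clinical information alongside. The Effectiveness section speaks of basic descriptive statistics and claims no causal effect. If completers do have higher follow-up TTR, for whatever reason, a test that detects it is not in error. This stands in part: the rejection rates above are false positives only for a difference beyond baseline. But the comparison is still tested for significance, under a heading that invites the reader to credit self-management, so the baseline-adjusted difference is the more informative one.

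Other points also stand:

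- **No TTR gap is documented.** A reader might infer from the progression rule and the Reach comparison that the plan expects completers to have had better INR control. It does not say so. Prior TTR is not named as a progression criterion, all participants must be medically stable and already self-testing, and comparing baseline characteristics is routine.
- **Pre-study INR control is not ignored throughout.** The paired before/after analysis uses it; only the between-group test leaves it out.
- **The precision gain may be smaller than shown.** Participants who stop early may have shorter INR series, giving noisier TTR and a weaker correlation.
- **The larger threat lies elsewhere.** Completion is a post-baseline event that INR control during follow-up may itself influence. Pre-study TTR cannot repair that.

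**Conclusion.** The point holds in a limited form. The protocol fixes an unadjusted between-group test of follow-up TTR although the outcome's own 6-month baseline is obtainable for every participant. Earlier differences in INR control can therefore appear as a transition-group difference, and precision is lost. Under an assumed SD of 20 and correlation of 0.3 to 0.7, the standard error would be about 5% to 29% lower with adjustment when there is no gap. A pre-study gap of 5 to 10 points would carry over about 1.5 to 7 points if it regresses by the correlation. Gap, SD, correlation and split are all assumptions.

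Two stronger conclusions are tempting, and the protocol supports neither. One is that the planned test will produce a spurious result: that needs a baseline gap nobody has shown. The other is that adjustment yields an unbiased effect of self-management: a persisting gap leaves about (1 − r)D, and the grouping is still defined by what happens after baseline. The primary Reach percentages are untouched, so this is a worthwhile improvement to a secondary analysis rather than a threat to the study.

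**What to change.** In the Effectiveness section:

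1. Replace the between-group t-test for TTR with a linear model of follow-up TTR on transition status, with pre-study 6-month TTR, site and goal INR range as covariates. Report the adjusted difference with its 95% CI; the unadjusted group means can stay as description.
2. Adjust the dose-change proportion for its own pre-study value in a model suited to a proportion, for example a binomial model of dose changes out of INRs that allows for over-dispersion.
3. State that both results are associations. Adjustment reduces baseline confounding but need not remove it, and transition status is a post-baseline event that INR control may influence.

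The cost is a change of analysis wording. The pre-study INRs and doses, site and goal range are already collected, and neither the sample size nor the primary outcome changes.

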#### **Discussion**

This study is designed to answer an important question regarding the feasibility of warfarin PSM implementation in the US healthcare system. While PSM is recommended as the preferred warfarin management strategy by evidence-based guidelines it is virtually unused in the US healthcare system despite being widely used elsewhere in the world. Our study team members previously identified addressable barriers to and potential facilitators of wider PSM

implementation from the perspective of US patients receiving warfarin and clinicians who manage them. The results of these earlier qualitative studies were used in the rationale and design of the protocol for this implementation study. Our study is intended to demonstrate the feasibility of PSM implementation in the US healthcare system and generate an implementation toolkit for use by others interested in exploring PSM use at their clinical sites.

This study will be among the largest to assess the feasibility of PSM implementation in US settings and the first to use an implementation toolkit specifically designed to address barriers and incorporate facilitators previously identified through qualitative focus groups and interviews with US clinicians and patients, respectively. To our knowledge only three small studies evaluating PSM in the US have been conducted to date. The planned enrollment of 150 patients for our study will exceed that of all previous US-based studies combined.

The proposed study will provide crucial information on the characteristics of patients likely to be interested in attempting PSM, the performance of PSM patient educational tools, the usability of clinical decision support tools, the capability of US patients to safely engage in PSM, and the acceptability of PSM workflows in US healthcare settings.

We chose the RE-AIM framework as it has been shown to highlight essential program elements including external validity that can improve the sustainable adoption and implementation of effective, generalizable, evidence-based interventions like PSM. Further, we chose to utilize anticoagulation management services that have achieved Anticoagulation Centers of Excellence status as defined by the Anticoagulation Forum based on the premise that successful PSM implementation at these sites will promote dissemination of PSM implementation strategies to other centers throughout the US.

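### A non-significant McNemar test on bleeding and thromboembolic events says little about safe self-management at 150 patients; interval estimates should carry that reading

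*Protocol*

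**What the plan says.** The Effectiveness section of the Protocol places the clinical events in a before/after contrast: "Additional effectiveness outcome comparisons before and after PSM transition will include major bleeding and clinically relevant non-major bleeding events", with thromboembolic events and all-cause mortality in the same sentence. For before/after outcomes the method is: "Paired t-tests and McNemar's test will be used to compare differences between continuous and categorical outcomes before and after PSM transition, respectively". The threshold is: "Two-sided P-values <0.05 will be considered statistically significant". Whether McNemar's test is to be exact or asymptotic is not stated.

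Two other statements in that section bear on the point. Effectiveness "outcomes will consist of basic descriptive statistics", so event summaries are also planned. And "T-tests and the chi-squared test of association will be used to compare differences in continuous and categorical outcomes" concerns participants who do and do not transition successfully; the outcomes listed for that contrast are the INR control outcomes, not the clinical events.

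The Discussion counts "the capability of US patients to safely engage in PSM" among the things on which the study will provide information. It gives the size as 150: "The planned enrollment of 150 patients for our study will exceed that of all previous US-based studies combined". The Protocol states no expected event rate, margin or power for the clinical events.

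**The concern.** McNemar's test asks whether the data contradict no change. When events are few it will usually fail to do so, whether or not harm has risen, so p above 0.05 is close to uninformative. The Protocol nevertheless pairs an interest in safe engagement with a significance threshold as its one inferential criterion for the events. A report that follows the plan could show no significant change in bleeding or thromboembolism, and readers could take that as reassurance while the data remain compatible with a substantial increase. This matters because the study is meant to encourage other centres to take up PSM.

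**Working it through.** There is no power or event-rate figure in the Protocol to reproduce. The check asks how often the stated test would miss a true doubling of risk.

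**Inputs from the Protocol.** N = 150, used as 150 complete pairs, which is the best case. Two-sided 0.05. McNemar's test, version unstated. Six months each side: "INR control outcomes will also be compared between the 6-month periods before and after PSM transition attempts". That length is given for INR control and is assumed here to hold for events too.

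**Assumptions.** 6-month risk before PSM, p, from 0.5% to 10%; risk after PSM 2p; the two periods independent within a person.

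**Formulas.** Event only before: b = p(1 − 2p). Event only after: c = 2p(1 − p). The number of discordant pairs D is Binomial(150, b + c). Given D, the number after-only is Binomial(D, c/(b + c)). Power is the total probability of outcomes with p < 0.05 in the harmful direction, summed exactly; the miss rate is 1 minus power.

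**Worked case, p = 1%.** b = 0.01 × 0.98 = 0.0098 and c = 0.02 × 0.99 = 0.0198, so b + c = 0.0296 and the expected D is 150 × 0.0296 = 4.4. The exact test cannot reach p < 0.05 with fewer than 6 discordant pairs: 5 against 0 gives 2 × 0.5^5 = 0.0625, and 6 against 0 gives 2 × 0.5^6 = 0.031. In the typical data set significance is out of reach.

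**Worked case, p = 5%.** b = 0.05 × 0.90 = 0.045 and c = 0.10 × 0.95 = 0.095, so the expected D is 150 × 0.14 = 21.

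| Risk before → after | Missed, exact | Missed, asymptotic |
|---|---|---|
| 0.5% → 1% | 99.8% | 96.9% |
| 1% → 2% | 97.8% | 90.8% |
| 2% → 4% | 90.8% | 84.8% |
| 3% → 6% | 84.0% | 77.7% |
| 5% → 10% | 70.4% | 61.4% |
| 8% → 16% | 50.4% | 42.3% |
| 10% → 20% | 37.4% | 31.7% |

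**Sensitivity.**
- With 120 complete pairs, the miss rates are 98.8% / 92.9% at 1% and 76.7% / 69.0% at 5% (exact / asymptotic).
- If half of those with an event before also have one after, the miss rates at 5% fall to 59.5% / 50.4%. At 1% this correlation gives no such relief: exact power is 1.3%, against about 2.2% under independence.
- Pairs needed for 80% power, from n = [1.96√ψ + 0.84√(ψ − δ²)]²/δ² with ψ = b + c and δ = p: about 2,320 at 1%, 1,140 at 2% and 440 at 5%.

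**What p > 0.05 hides.** With 6 participants having an event only after and 3 only before, exact p = 0.51, yet the matched ratio is 2.0 with exact 95% CI 0.43 to 12.4. With 10 against 5, p = 0.30 and the ratio is 2.0 (0.62 to 7.5). With 0 events in 150 on PSM, the upper limit is 1 − 0.025^(1/150) = 2.4%.

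**The case against.** The strongest reply has four parts.

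- **No rule equates non-significance with safety.** A reader might infer from the threshold and the Discussion that p above 0.05 will be reported as safe. The Protocol does not say so. It defines only what counts as significant, and it plans descriptive statistics as well. This stands.
- **The design does not claim power for events.** In a type III hybrid the primary outcome is Reach, and clinical outcomes are gathered alongside it. Other material also bears on safe engagement: clinician review of the INR surveys, the share of INRs managed independently and appropriately, reasons for and timing of PSM failures, and clinicians' views on continuing PSM. This stands too. Low power here is no design fault and no case for a larger sample. It is the reason to prefer estimation to a significance test.
- **The size rests on assumed rates.** A reader might take a miss rate above 60% as established. It holds only for baseline risks up to about 5% under independence. Higher risks, conceivable for non-major bleeding, bring it down to a third or a half.
- **Intervals could be in a statistical analysis plan that is not shown.** Their absence from the Protocol is therefore not an error. The point concerns the criterion that the Protocol does state.

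An interval also does not cure the design. There is no concurrent control, and enrolment requires medical stability and more than 9 months of warfarin, so the before period may be selected for few events.

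**Conclusion.** The point holds in a limited form. The one inferential criterion stated for before/after bleeding and thromboembolic events cannot inform the interest in safe engagement when it is non-significant, and non-significance is likely even after a doubling of risk: about 61% to 99.8% at assumed baseline risks of 0.5% to 5%, and about 32% to 50% at 8% to 10%, with 150 complete pairs and independent periods. Fewer pairs raise these figures. Positive within-person correlation lowers them where events are not very rare. What follows is a risk of misinterpretation, not an error in the primary analysis, which is unaffected. It should be corrected because the wording change is small and the event results are likely to be read as safety evidence.

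**What to change.** In the Effectiveness section, for major bleeding, clinically relevant non-major bleeding and thromboembolic events:

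1. Make the main analysis the event counts, the paired risk difference (after minus before) with a 95% CI from a method valid for sparse paired data, and the on-PSM 6-month event proportion with an exact 95% CI. A score or exact interval serves for the difference. A Wald interval does not, because it shrinks to zero width when there are no discordant pairs.
2. Keep McNemar's test as supportive only.
3. State that a non-significant result will not be reported as evidence of safety, and that any safety statement will cite the upper limit, that is, the largest increase not excluded.
4. Note that the uncontrolled before/after contrast limits interpretation.

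All-cause mortality needs separate handling: everyone enrolled survived the before period, so a paired before/after comparison has no meaning for it.

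The cost is wording and a few extra estimates; no new data or participants are needed. The price is a less favourable safety statement, because the limits will be wide.
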